## Human Subjects Research Protocol

The Common Human Subjects Protocol Cover Form **must** be completed and **attached** to the front of this form. This Protocol form should be completed for any human subjects research proposal that does not have a specific "protocol," such as a grant application. This form must be submitted along with a copy of the complete grant proposal and all the information in this form **must** be consistent with that proposal. This protocol form, once IRB approved, will be the working protocol for that research. **When completing this document, do not refer to page numbers within your grant.** If revisions are necessary during the course of the research, amendments should refer to this protocol form, not the grant proposal. Enter responses for all sections. Check N/A if the section does not apply.

### PROTOCOL SUMMARY

Project Title:

Protocol Version Date:

Smartphone-based Financial Incentives to Promote Smoking Cessation Among Pregnant Women

4/2/2020

Principal Investigator: [name].

Grant Sponsor: NIGMS

Grant Number: 4P20GM103644-04

(For grants routed through UVM, indicate the OSP Proposal ID # located at the top of the OSP Routing Form)

**Lay Language Summary:** (Please use non-technical language that would be understood by nonscientific IRB members to summarize the proposed research project. The information must include: (1) a brief statement of the problem and related theory supporting the intent of the study, and (2) a brief but specific description of the procedure(s) involving the human subjects. Please do not exceed one single-spaced 8 ½ X 11" page.)

Cigarette smoking during pregnancy increases risk for catastrophic pregnancy complications, growth retardation, other adverse fetal and infant health problems, and later-in-life chronic conditions among exposed offspring. The most effective intervention for reducing smoking during pregnancy is financial incentives whereby participants earn incentives (e.g., gift cards, cash) contingent on objective evidence of smoking abstinence. However, financial incentives-based interventions are typically delivered in relatively intense protocols requiring frequent clinic visits, which limits the geographical range over which services can be delivered and potentially denies treatment to those residing in remote or otherwise difficult to reach settings.

The present study will examine the feasibility, efficacy, and cost-effectiveness of a smartphone-based financial incentives intervention whereby smoking monitoring and delivery of incentives are completed remotely using a mobile app (to be designed by DynamiCare Health, Inc.). Pregnant women will be recruited via obstetrical clinics, WIC offices, and ads in print and online media outlets in all Vermont counties, and in obstetrical clinics and WIC offices outside Vermont. Eligible participants who complete the informed consent process will be randomized to one of two conditions: an incentives condition wherein women will receive financial incentives contingent on the remote submission of breath and saliva specimens indicating abstinence from recent smoking (described below), or a best practices control condition in which women will receive usual care for smoking cessation that is provided at their obstetrical clinics, as well as three brief educational sessions and referral to the Vermont (or other state) pregnancy-specific quit line by our research staff. This is the same control condition that we are using in our current ongoing cost-effectiveness trial (CHRMS 13-143).

For inclusion in the study, women must meet the following criteria: (a)  $\geq 18$  years of age, (b) report being smokers at the time they learned of the current pregnancy, (c) report smoking in the 7 days prior to completing their phone eligibility screening, (d)  $\leq 25$  weeks pregnant, (e) speak English, (f) own a smartphone (Android or iOS; 81.8% of pregnant women in wave 1 [2013-2014] of the Population Assessment of Tobacco and Health [PATH] reported owning a smartphone). Exclusion criteria include: (a) current or prior mental or medical condition that may interfere with study participation (assessed via self-report during phone eligibility screening), (b) smoke marijuana more than once each week and not willing to quit (marijuana smoking can inflate breath CO), (c) exposed to unavoidable occupational sources of CO (e.g., car mechanic), and (d) self-report currently being maintained on

Participants randomized to the incentives condition will select a quit date (either the first or second Monday following their enrollment), and will submit videos of themselves blowing into a breath CO monitor twice daily during week 1. They will receive incentives for every sample where expired breath CO is  $\leq 6$  ppm. Beginning in week 2 and extending through week 6, participants will submit videos twice per week (Monday/Thursday) for which they will receive incentives for providing videos of themselves completing saliva cotinine tests indicating smoking abstinence. From week 7 until delivery, participants will submit videos once per week and will continue to receive incentives for saliva cotinine tests indicating no smoking. During the postpartum period, women will submit videos twice weekly for the first 4 weeks and once weekly from weeks 5-12. The first negative breath CO or salivary cotinine sample is worth \$6.25 and each consecutive negative sample will increase the value of the incentive by \$1.00 up to a maximum of \$33.25 per sample. Missed samples or samples that indicate smoking will be worth \$0 and will reset the incentive at its starting value. However two consecutive negative samples following the slip will restore the incentive to its value before the slip. The maximum earnings in this condition is \$1,620, which is the same as our prior studies adjusting for inflation. A proposed voucher schedule is attached.

Women in both conditions will complete seven formal assessments of their smoking status during their participation (intake, early pregnancy or 1 month after enrollment, late pregnancy or  $\geq 28$  weeks gestation, and at 4-, 8-, 12-, and 24-weeks postpartum) along with a treatment acceptability questionnaire and semi-structured interview on barriers and facilitators of treatment engagement. Women will receive \$50 for completing each of these (\$400 total)

We conducted a power analysis to estimate the number of participants required to detect treatment effects assuming late-pregnancy abstinence rates of approximately 40% vs.  $< 10\%$  (incentives vs. best practices, respectively), and 24-week postpartum abstinence rates of approximately 20% vs.  $< 5\%$ . These abstinence rates are based on data from our current trial and previous trial data indicating a 20% decrease in abstinence rates from late pregnancy to 24-weeks postpartum. The proposed sample size of 76 per treatment condition will result in at least 80% power to detect a difference between the two treatment conditions in abstinence rates of 40% vs. 10% at late-pregnancy or 20% vs. 5% at 24-weeks postpartum assessments using a chi-square test and significance level of 0.05.

Pregnant women will be recruited via obstetrical clinics, WIC offices, and ads in print and online media outlets in all Vermont counties, and in obstetrical clinics and WIC offices outside Vermont. Recruitment materials that we propose distributing at these sites are attached. We have also attached the battery of questionnaires that we propose administering at formal assessments, as well as the Research Information Sheet that we will read to participants over the phone to obtain verbal consent to participate in the study, as well as the full consent form that we will mail to them after obtaining their verbal consent to participate.

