biochemical verification of smoking status, which limits access to those in the immediate vicinity of clinics that can provide such care. ***Capitalizing on technological advancements may surmount such access barriers, with the potential to extend the reach of financial incentives to disadvantaged pregnant smokers nationwide.***

**The overarching aim of the current study is to develop an innovative, efficacious, remotely delivered financial incentives intervention to reduce cigarette smoking during pregnancy.** To enable flexible use of the intervention in diverse locations, we will use a mobile-phone-based platform for delivering the incentives intervention. Recent data indicate that over 80% of pregnant women drawn from a U.S. nationally representative sample own a smartphone. The platform will involve a Smartphone “app” which uses video capture to verify smoking status via a breath carbon monoxide (CO) monitor along with saliva cotinine test kits, and ensures treatment fidelity by providing automated, immediate feedback, incentive calculations, and incentive delivery for abstinence. Comparable technology-based treatment delivery platforms have been used to successfully promote smoking abstinence among the general population of U.S. smokers and among other vulnerable populations including rural heavy smokers.

The proposed study addresses the following specific aims:

**Aim 1:** Examine the feasibility, efficacy, and cost-effectiveness of a mobile-phone-based incentives intervention for promoting smoking cessation among economically disadvantaged (i.e., Medicaid insured) pregnant women. We will accomplish this aim by randomly assigning 152 pregnant women who are still smoking at their first prenatal care visit to receive incentives contingent on biochemically verified smoking abstinence or best practices for promoting smoking cessation. Incentives will be in place from the start of prenatal care through three months postpartum. Primary outcomes will be point prevalence smoking abstinence, continuous abstinence during and following pregnancy, and birth outcomes (mean birth weight, gestational age, NICU admissions). We hypothesize that there will be higher abstinence rates, longer durations of abstinence, and improved birth outcomes in the incentives versus the best practices condition.

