[PATH] reported owning a smartphone). Exclusion criteria include: (a) current or prior mental or medical condition that may interfere with study participation (assessed via self-report during formal intake assessment completed online or by phone using a medical and psychosocial history questionnaire), (b) smoke marijuana more than once each week and not willing to quit (marijuana smoking can inflate breath CO), (c) exposed to unavoidable occupational sources of CO (e.g., car mechanic), (d) report currently receiving opioid maintenance therapy (e.g., methadone, buprenorphine). Women who meet the inclusion criteria and complete the informed consent process will be considered formally enrolled and will be mailed equipment to participate in the study, but will not be randomized until they (1) confirm receipt of their equipment, (2) complete an orientation session on the smartphone app used in the current study (described subsequently), and (3) provide a saliva sample indicating current smoking (i.e., test strip returns a positive for cotinine, a metabolite of nicotine). Upon completing these steps, women will be randomized to either the incentives or best practices treatment condition (See Treatment Conditions). The only criteria for withdrawing participants after randomization occurs will be pregnancy termination or fetal demise.

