#### **Statistical Methods**

Study conditions will be compared on baseline demographics and other characteristics using analysis of variance (ANOVA) for continuous variables and chi-square tests for categorical variables. If a specific characteristic differs significantly across study conditions and is predictive of the outcome, it will be considered as a potential covariate in subsequent analyses. Analyses of treatment effects on smoking status will adhere to an intent-to-treat approach whereby all women randomized to each study condition will be included in the analyses independent of early dropout, noncompliance, etc., with the exception of women excluded for abortion/fetal demise as is convention in this research area. Cochran-Mantel-Haenszel tests (C-M-H) will be performed for comparisons between the incentives vs. usual care conditions on point-prevalence smoking abstinence at end-of-pregnancy and 6-months postpartum assessments with referring clinic as a stratification variable. The Breslow-Day Test will be used to examine the homogeneity of treatment effects across referring clinics. Comparisons of point-prevalence abstinence rates between treatment conditions across all assessments through six months postpartum will be analyzed using mixed model repeated measures for categorical data based on generalized estimating equations (GEE) using a logistic link function (SAS: PROC GENMOD, SAS Institute, Cary, NC). The two treatment groups will also be compared on birth outcomes, breastfeeding, and other measures collected postpartum. Comparisons of treatment conditions on dichotomous outcomes (e.g., % low birth weight, % preterm, % NICU admissions, % breastfeeding) will parallel categorical analyses for point prevalence abstinence using PROC GENMOD to adjust for strata (referring clinics) and potential covariate effects. Analysis of covariance (ANCOVA) will be used to compare study conditions on mean birth weight adjusting for variables known to influence birth weight (% maternal pre-pregnancy BMI, parity, and sex) and mean gestational age at delivery. The significance criterion will be set at  $\alpha = 0.05$  for all analyses.

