Women will be free to withdraw at any point during the course of the study without penalty. That will be explained during informed consent. In terms of data analysis, we will adhere to an intent-to-treat approach (Armitage, 1983) wherein all women randomized to the study conditions will be included in the analyses independent of early dropout, noncompliance, etc., with the exception of excluding women for abortion/fetal demise as is convention in this research area. Women who receive their equipment and fail to complete an orientation session, as well as women who provide a baseline CO sample indicating that they are non-smokers, will be withdrawn prior to randomization and thus not included in an intent-to-treat analysis.

**Sources of Materials:** Identify sources of research material obtained from individually identifiable human subjects in the form of specimens, records or data. Indicate whether the material or data will be obtained specifically for research purposes or whether use will be made of existing specimens, records or data.

The research materials to be obtained include interviews, questionnaires, breath and saliva specimens to verify smoking status (and serve as the basis for reinforcement in the incentives condition), and medical records to assess birth outcomes. Materials will be collected remotely using a combination of phone calls with participants, online surveys, and remote video capture via smartphone app (i.e., for submission of breath CO samples and salivary cotinine samples). Delivery reports will be obtained via fax and entered into databases with no identifying information (i.e., with subject ID only). These databases are stored on password-protected external hard drives in locked offices in a locked clinic accessible only to the PI and research staff.

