**Not applicable**

Pregnant women and their infants to develop more effective interventions to help them quit smoking and to examine improvements in birth outcomes from doing so.

**Number of Subjects:** What is the anticipated number of subjects to be enrolled at UVM/UVM Medical Center and in the case of a multi-center study, with UVM/UVM Medical Center as the lead, the total number of subjects for the entire study.

152 women and their infants in the main trial plus 60 AI/AN women and their infants recruited at a different site (ANTHC, Anchorage, AK) = 424 subjects total.

**Inclusion/Exclusion Criteria:** Eligibility and ineligibility criteria should be specific. Describe how eligibility will be determined and by whom. Changes to the eligibility criteria at a later phase of the research have the potential to invalidate the research.

A total of 152 Mom's will be recruited for the main trial plus 60 AI/AN women recruited at our collaborating site (ANTHC, Anchorage, AK). Participants will be healthy, socioeconomically disadvantaged (i.e., Medicaid insured) pregnant smokers. The inclusion criteria include: (a)  $\geq 18$  years of age, (b) report being smokers at the time they learned of the current pregnancy, (c) report smoking in the 7 days prior to completing their phone eligibility screening, (c)  $\leq 25$  weeks pregnant, (d) speak English, (e) own a smartphone (Android or iOS; 81.8% of pregnant women in wave 1 [2013-2014] of the Population Assessment of Tobacco and Health [PATH] reported owning a smartphone). The exclusion criteria include: (a) current or prior mental or medical condition that may interfere with study participation, (b) smoke marijuana more than once each week and not willing to quit (marijuana smoking can inflate breath CO), (c) exposed to unavoidable occupational sources of CO (e.g., car mechanic), and (d) currently maintained on opioid maintenance therapy. The only criteria for withdrawing someone from the trial following randomization to treatment condition will be pregnancy termination or fetal demise. Women who fail to complete an orientation session or provide an initial CO sample indicating that they are smokers will be withdrawn prior to randomization. Criteria will be assessed during a phone screen to determine preliminary eligibility and further evaluated during the formal intake assessment.

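### The protocol counts its 152 women both at randomisation and at enrolment (consent); if 152 is applied at consent, the 24-week claim of at least 80% power has little margin to absorb the shortfall

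*Protocol*

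**What the plan says.** **Power claim.** The Protocol Summary says "The proposed sample size of 76 per treatment condition will result in at least 80% power to detect a difference" for "abstinence rates of 40% vs. 10% at late-pregnancy" or "20% vs. 5% at 24-weeks postpartum assessments using a chi-square test and significance level of 0.05". The Sample Size Justification repeats this and adds that the tests are two-sided.

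**Where 152 is counted.** Aim 1, under Purpose, speaks of "randomly assigning 152 pregnant women who are still smoking at their first prenatal care visit", which makes 152 (76 per arm) a randomised count. The Number of Subjects section, where the form asks how many subjects will be enrolled, answers "152 women and their infants in the main trial plus 60 AI/AN women and their infants recruited at a different site". The Inclusion/Exclusion Criteria section calls the same 152 recruited.

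**What enrolment means.** The Participants section states: "Women who meet the inclusion criteria and complete the informed consent process will be considered formally enrolled". Randomisation comes only after equipment is received, orientation is completed and a saliva sample confirms smoking.

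**Who is removed.** Under Withdrawal Procedures, women who receive equipment but do not complete orientation, or whose baseline sample shows no smoking, "will be withdrawn prior to randomization and thus not included in an intent-to-treat analysis". The Participants, Orientation Session and Inclusion/Exclusion sections carry similar rules. After randomisation, the Statistical Methods keep every woman in the analysis, including dropouts, "with the exception of women excluded for abortion/fetal demise as is convention in this research area". No section gives a rate for either kind of removal or adjusts 76 or 152 for it.

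**The concern.** The 152 appears at two stages that are separated by a step at which women are removed. If any enrolled woman fails orientation or smoking verification, 152 enrolled cannot become 152 randomised. The protocol expects some failures, since it writes rules for them.

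Two things depend on this. One is when recruitment stops: a team working to the enrolment figure given to the IRB would stop short of the number on which the power claim rests. The other is how a non-significant 24-week result is read. That comparison sets the sample size and has almost no spare power, so a modest shortfall decides whether the stated 80% is met.

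**Working it through.** **Inputs.** 76 per arm; 20% vs 5% at 24 weeks; 40% vs 10% at late pregnancy; chi-square test; significance level 0.05 (Protocol Summary). Two-sided (Sample Size Justification). Equal allocation (Consent Procedures). Loss rates are not in the protocol; those below are assumptions.

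**Step 1: reproduce the stated figure.** Usual chi-square formula, pooled variance under the null, no continuity correction, mean rate 0.125:

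n per arm = [1.96·√(2·0.125·0.875) + 0.8416·√(0.2·0.8 + 0.05·0.95)]² / 0.15²
= (0.9167 + 0.3834)² / 0.0225 = 75.1, rounded up to 76.

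Power = Φ{[0.15·√n − 0.9167] / √0.2075}:
- n = 76: Φ(0.858) = 80.5%
- n = 75: Φ(0.839) = 79.9%

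The stated claim is therefore correct at 76 analysed per arm, and by this formula 76 is the smallest number that supports it. The late-pregnancy comparison needs 32 per arm and has 99.3% power at 76, so the 24-week comparison drives the size.

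**Step 2: check against other methods.** Exact enumeration of the uncorrected Pearson chi-square, using the 3.841 critical value, gives 83.3% at 76. Other approximations need fewer women (73 per arm unpooled, 70 arcsine). A continuity correction needs 88, and exact power at 76 with the Yates correction or Fisher's test is 76.7%. The protocol does not say which version it used. The named test without correction fits the stated number.

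**Step 3: power at smaller analysed numbers (20% vs 5%).**

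| Per arm analysed | Assumed loss from 76 | Usual formula | Exact uncorrected chi-square |
|---|---|---|---|
| 76 | none | 80.5% | 83.3% |
| 75 | one woman | 79.9% | 82.7% |
| 72 | about 5% | 78.3% | 81.0% |
| 71 | about 7% | 77.7% | 80.4% |
| 70 | about 8% | 77.1% | 79.8% |
| 68 | about 10% | 75.9% | 78.6% |
| 61 | about 20% | 71.2% | 73.8% |

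At 61 per arm the late-pregnancy power by the usual formula is still 97.7%.

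**Step 4: apply the two readings.**
- *152 applied at consent.* Both the pre-randomisation withdrawals and the pregnancy-loss exclusion reduce the analysed number. A combined loss of 10% gives about 76-79% power, and 20% gives about 71-74%.
- *152 randomised.* Pre-randomisation withdrawals cost no power. Only pregnancy termination or fetal demise reduces the analysed number. A 5% loss gives 78.3% by formula or 81.0% exact.

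**The case against.** The stated figure reproduces, so there is no arithmetic error. Aim 1 refers to random assignment, and a number per treatment condition makes sense only after randomisation. Women withdrawn earlier are expressly outside the intent-to-treat set. The enrolment figure answers an IRB form's headcount question, and recruited is not the term that the protocol defines. All of this stands. It supports the randomised count as the basis of the power claim, but it does not remove the conflict with the enrolment figure read under the protocol's own definition.

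The usual inflation for dropout is not needed, because dropouts stay in the analysis. That also stands.

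The planning text expects control abstinence below 5% and computes power at 5%. At 20% vs 4.5% the usual formula gives 83.7% with 76 per arm and 80.6% with 70; at 20% vs 4% it gives 86.6% with 76 and 82.6% with 68. So there is some margin if the control rate is lower. The power claim itself, however, is made at 5%.

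A reader might infer that the protocol definitely counts its 152 at consent, and so fails to deliver its stated power. The documents do not support that. Aim 1 says otherwise, no loss rate is given, and the larger shortfalls need both the consent reading and assumed losses of roughly 10-20%.

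**Conclusion.** The protocol places 152 at two incompatible points, and this needs reconciling because it decides when recruitment stops. The 24-week claim of at least 80% power is true for 76 analysed per arm but has little or no margin: one woman per arm by the usual formula, and down to 71 per arm by exact chi-square.

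The consequence depends on the reading. At consent, power is about 76-79% with 10% lost and 71-74% with 20% lost. At randomisation, the shortfall is small or nil: 78.3% or 81.0% with 5% lost to the pregnancy-loss exclusion. Every loss rate here is an assumption, and the results assume true rates of 20% and 5%. The late-pregnancy claim stands under either reading.

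**What to change.** In the Participants, Number of Subjects and Inclusion/Exclusion sections, state that 152 (76 per arm) is the number randomised in the main trial. Give the number to be consented separately, large enough to cover withdrawals before randomisation.

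In the Protocol Summary and the Sample Size Justification, say that the 24-week figure of at least 80% applies to 76 analysed per arm. Name the calculation method, and show power over a range of assumed pregnancy-loss exclusions, labelled as assumptions. A single replacement power figure should not be written in, because the protocol has no loss rate to support one. The late-pregnancy statement can stay.

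The cost is a wording amendment. The approved consent count rises, and the stated 24-week power looks slightly less favourable. The randomised target in Aim 1 does not change.
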